# STUDY OBJECTIVES and related endpoints

## Primary Endpoint

| Phase 1: Milligrams of benzodiazepines (oxazepam) used to complete 3 days of detoxification and Actigraph-assessed akathisia and sleep.  Phase 2: Time to ‘relapse’ and amount of alcohol intake during 4 weeks of subsequent outpatient treatment. |
| --- |

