# STUDY procedures

## Flow Chart

Table 1. Trial flow chart

|  | **In-patient period (day)** | | | **Outpatient Period (day)** | |
| --- | --- | --- | --- | --- | --- |
| **Time** | **On arrival**  **D 1** | **D 2** | **Discharge**  **D 3** | **D 30** | **D 60** |
| Informed consent | X |  |  |  |  |
| Inclusion/exclusion  Evaluation | X |  |  |  |  |
| Medical History, record of concomitant medication | X |  |  | X |  |
| Prior treatment | X |  |  |  |  |
| Physical Examination^1)^ | X |  |  |  |  |
| Vital signs, CIWA-Ar ^2)^ | X | X | X | X |  |
| Blood samples^3)^ | X |  | X | X |  |
| Urine samples^4)^ | X |  | X | X |  |
| Actigraph | X | X | X |  |  |
| Staff administered nasal spray | X | X | X |  |  |
| Self-reported sleep | X | X | X | X |  |
| Alcohol Craving Experience Questionnaire(ACE), SCL-10, PAM-13^5)^ |  |  | X | X |  |
| RMET^6)^, dot-probe-task^7)^ |  | X | X | X |  |
| Self-administered and reported use of nasal spray, relapse to drinking and weighing of spray bottles |  |  |  | X |  |
| Alcohol consumption (Time-Line Follow-back^8)^, Days until relapse, Daily quantity of standard alcohol units, Number of binge drinking episodes, self-reported intake of benzodiazepines |  |  |  | X |  |
| Phone interview with AUDIT^9)^ |  |  |  |  | X |

1. Cor/pulm/abdomen and peripheral lymph node status and neurology with emphasis on alcoholic damage to the cerebellum and signs of Wernicke/Korsakoffs syndrome.
2. Blood pressure, pulse, temperature, weight, alcohol expiration test until 0‰ x 2. CIWA-Ar after symptom driven protocol
3. Once daily: CRP, Hb, HCT, WBC (incl.differential counting, Na, K, Ca, glucose, creatinine, ALAT, LD, ALP, γGT, INR, albumin, bilirubin, p-oxytocin, CDT, PEth.
4. Once daily: Toxicology screening: urine dipstick and laboratory tests (incl. the ethanol metabolites EtG and EtS. (Pregnancy test (HCG) at admittance in fertile women).
5. See chapter 7.3 Other assessments
6. See chapter 7.3 Other assessments
7. See chapter 7.3 Other assessments
8. See chapter 7.3 Other assessments
9. See chapter 7.3 Other assessments

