**Time-Line Follow-back**

A visual tool helping patients to remember events the previous 30 days ^24^.

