## Statistical Analysis

Statistical analysis will be performed by Unit for Applied Research, NTNU.

Descriptive data will be presented as mean ± SD. Dichotomuos outcome variables will be compared using non-parametric test (paired Wilcoxon signed rank test, and McNemar´s test). P-values <0.05 will be considered significant.

0-hypothesis: Oxytocin nasal spray does not differ from placebo in reducing alcohol withdrawal symptoms or decrease craving after detoxification

Primary hypothesis 1: Oxytocin nasal spray can reduce the amount of oxazepam needed to complete 3 days of alcohol detoxification.

Primary hypothesis 2: Oxytocin nasal spray can decrease craving the subsequent 4 weeks after detoxification.

Group comparisons of oxazepam use (measures in mg) at 3 days will be done with student t-test. We will use mixed‐effects regression analyses to examine the change in sleep and actigraph scores from D1 to D3, and changes in anxiety, depression and alcohol use from discharge (D3) to follow-up (D30). Statistics will be performed with per-protocol and intention-to-treat data.Mixed methods take the correlation among repeated measures into account, and they use all available data, thereby lessening concerns about missing data. The basic model will include group (oxytocin, placebo) as the between‐subjects factor and time as the repeated measure. The treatment effect will be evaluated as the group by time interaction, according to the planned comparisons. Both group and time will be fixed‐effects. Covariates can also be added to the models, in order to partial out their effects before evaluating the treatment effects. Follow‐up t‐tests and other post hoc methods will be used to test more time‐ and group‐specific hypotheses. We will test primary hypotheses at the .05 level of significance, but follow‐up and exploratory analyses will be tested at the .01 level of significance.

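### Section 10.4 analyses alcohol use as a change from D3 to D30 although there is no informative D3 value, and no method it names suits time to relapse

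*Protocol*

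**What the plan says.** **Endpoints.** Protocol section 2.1 lists two phase 2 primary endpoints: time to relapse and "amount of alcohol intake during 4 weeks of subsequent outpatient treatment". The endpoints row of the synopsis agrees. The objectives row of the synopsis puts the same measures under the third secondary aim, and the second primary hypothesis in section 10.4 is about craving.

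**Analysis.** Section 10.4 uses mixed-effects regression to examine "changes in anxiety, depression and alcohol use from discharge (D3) to follow-up (D30". The basic model has "group (oxytocin, placebo) as the between‐subjects factor and time as the repeated measure", and "The treatment effect will be evaluated as the group by time interaction". The other methods named there are a t-test for oxazepam, the paired Wilcoxon and McNemar tests for dichotomous outcomes, and follow-up t-tests with unspecified post hoc methods.

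**Schedule.** In Table 1 (section 6.1) the alcohol row, with Time-Line Follow-back and "Days until relapse, Daily quantity of standard alcohol units, Number of binge drinking episodes, self-reported intake of benzodiazepines", is marked at D30 and nowhere else. D3 is discharge. SCL-10, by contrast, is marked at both D3 and D30.

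**Other sources of drinking data.** Patients receive a dated notebook at discharge, one page per day, for alcohol intake among other things (sections 5.5, 5.6 and 6.2.2). They hand it in at D30 (section 6.2.3). Time-Line Follow-back is described in section 7.3 as "A visual tool helping patients to remember events the previous 30 days". Drinking before admission is taken in the history and for the inclusion criterion on average daily consumption (sections 6.2 and 4.3).

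**The concern.** A change model needs an outcome value at both ends. For alcohol use, one end is the last day of a supervised inpatient stay, and no alcohol measure is scheduled there. The quantity that 10.4 calls the treatment effect is therefore either undefined or something other than a change. Time to relapse is a single value per patient, unobserved for anyone who has not relapsed by last contact, and it has no D3 value to change from.

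What is at stake is pre-specification. If the written analysis cannot be run as stated, someone must choose the intake measure, the window and the handling of patients not followed to D30 after the fact, in a trial of 40 patients and for endpoints that section 2.1 calls primary.

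**Working it through.** **The plan's own figure.** The only sample-size figure concerns oxazepam: a difference of 10 mg, SD 10 mg, alpha 0.05 and 80 % power (section 10.1). Two-sided normal approximation: 2 × (1.960 + 0.842)² × (10/10)² = 2 × 7.85 = 15.7, so 16 per group, as stated. It does not bear on phase 2, for which the protocol gives no figure.

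**The planned model.** Let G be 0 for placebo and 1 for oxytocin, and T be 0 at D3 and 1 at D30:

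E(Y) = b0 + b1·G + b2·T + b3·G·T, where b3 is the treatment effect.

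*Case 1: no D3 value.* Every row has T = 1, so the column for T equals the intercept and the column for G·T equals G. Only b0 + b2 and b1 + b3 can be estimated. The design matrix has rank 2 of 4, confirmed numerically with 20 patients per arm. The interaction b3 is not identified.

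*Case 2: D3 taken as 0 for every inpatient* (an assumption; the protocol does not say this). Then

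b3 = (mean oxytocin D30 − 0) − (mean placebo D30 − 0) = D30 group difference.

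In one simulated data set (20 per arm, both arms drawn from the same skewed distribution, so the difference is chance) the interaction was 1.946 and the plain D30 difference 1.946, each with SE 1.505. The D3 rows add no information and the result is not a change.

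*Case 3: daily notebook entries as the repeated measure.* Write mean intake on post-discharge day t in group g as a_g + c_g·t. The interaction is c_O − c_P, a difference in slope. Over 4 × 7 = 28 days the total is the sum for t = 1 to 28 of (a_g + c_g·t) = 28·a_g + 406·c_g, since 28 × 29 / 2 = 406. If the slopes are equal but the levels differ, the interaction is 0 while the 4-week totals differ by 28·(a_O − a_P). This model can be fitted, but its treatment effect is not the amount of intake over 4 weeks.

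**Time to relapse against the named methods.**

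- t-test: assigned to oxazepam, and it takes no account of censoring.
- Paired Wilcoxon and McNemar: tests for paired data, stated for dichotomous outcomes.
- Mixed model: needs repeated values, whereas there is one time per patient.

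None suits a possibly censored time.

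**Visit window.** The last visit may fall on D28 to D32 (section 5.6). The full days between discharge on D3 and a visit on day V number V − 4, that is 24 to 28. A rate per post-discharge day allows for this; a raw total does not.

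**The case against.** The strongest reply is that the X at D30 marks when data are retrieved, not the only day they describe. The notebook and Time-Line Follow-back give daily post-discharge intake, so a repeated-measures model with a group-by-time term can be estimated. The part about the data stands. A reader might infer that the phase 2 endpoints are lost, and the documents do not support that. What fails is the step to the analysis: case 3 shows that the interaction on daily data tests a slope. Case 2 is likewise a valid randomised comparison, but then it should be stated as one.

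Second, 10.4 speaks of alcohol use and never assigns time to relapse to the mixed model, and naming a survival method can be left to an SAP. Both statements are correct. Silence alone would be no finding. The narrower point is that the methods 10.4 does list include none that suits an endpoint section 2.1 calls primary.

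Third, CDT, PEth, EtG and EtS are measured at D3 and D30 and could be modelled as a change. They are not the stated endpoint, which is amount of intake.

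Two further stronger readings should be set aside:

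- Section 10.4 says of mixed methods that "they use all available data, thereby lessening concerns about missing data". A reader might infer that a patient who misses D30 contributes nothing. The documents do not go that far: section 6.2.4 provides three attempts at contact, and section 6.4.1 a final assessment at a visit or by phone where possible.
- A reader might infer that the 30-day recall window adds pre-admission drinking to the outcome. No section says the whole window is summed, and section 2.1 confines the endpoint to the outpatient weeks.

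Finally, the primary status of these endpoints is itself contradicted within the protocol, which limits the weight that can be put on the word.

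**Conclusion.** The point holds in a limited form. As written, the D3-to-D30 change analysis of alcohol use does not estimate the phase 2 intake endpoint. Its interaction is not identified without a D3 value, equals the D30 group difference if D3 is taken as 0, and is a slope difference if daily data are used. No method named in 10.4 suits time to relapse.

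The conclusion rests on Table 1 being the complete schedule for the alcohol measures and on reading discharge (D3) literally as the starting point. Pre-admission intake would be a sensible baseline, but 10.4 does not name it. No numerical bias or loss of power can be given from the protocol. The criticism does not reach anxiety or depression in the same sentence, because SCL-10 is taken at D3 and D30, nor the oxazepam comparison.

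**What to change.** In section 10.4:

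1. Remove alcohol use from the D3-to-D30 change model and leave anxiety and depression in it.
2. Compare drinks per day from discharge to the D30 visit between groups, from Time-Line Follow-back and the notebook, counting post-discharge days only and adjusting for the pre-admission daily intake recorded for eligibility.
3. Analyse time from discharge to first relapse by Kaplan-Meier and log-rank, censored at last contact, with a sensitivity analysis that counts patients lost to follow-up as relapsed. This requires the protocol to state what counts as relapse, which it does not do now.
4. Reconcile section 2.1 and the synopsis endpoints with the synopsis objectives and the second primary hypothesis, so that these endpoints have one status throughout.

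The changes are to wording and use data already planned. The D60 call should not be relied on to fill gaps, since its AUDIT interview covers only the preceding 30 days (section 7.3). The cost is slightly more analysis work.

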## Inclusion Criteria

All of the following conditions must apply to the prospective patient at screening prior to receiving study agent (e.g.):

- At least one prior episode 2 days or longer in duration during which the subject experienced withdrawal symptoms that caused significant incapacitation (e.g., inability to work or do normal activities) OR at least one prior inpatient or outpatient medical detoxification during which the subject exhibited withdrawal symptoms of sufficient magnitude that sedative-hypnotic or anticonvulsant medication was required at least once on 2 consecutive days after cessation of or reduction in the use of alcohol following 2 weeks or more of heavy daily consumption
- Average consumption of 8-30 standard drinks per day for at least 2 weeks prior to enrollment in the study
- Age 18-65
- Have residency inTrøndelag County after discharge
- Signed informed consent and expected cooperation of the patients for the treatment and follow up must be obtained and documented according to ICH GCP, and national/local regulations.

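### The amount-of-alcohol analysis tests a D3-to-D30 change with no scheduled D3 drinking value, and gives pre-admission drinking no committed role

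*Protocol*

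**What the plan says.** **Endpoint.** Protocol 2.1 (Primary Endpoint) lists "Phase 2: Time to ‘relapse’ and amount of alcohol intake during 4 weeks of subsequent outpatient treatment". The flow chart (6.1) names the measure as "Daily quantity of standard alcohol units", in a row marked at D30 only.

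**Model.** Protocol 10.4 (Statistical Analysis) plans mixed-effects regression for "changes in anxiety, depression and alcohol use from discharge (D3) to follow-up (D30"). It fixes the terms: "The basic model will include group (oxytocin, placebo) as the between‐subjects factor and time as the repeated measure". It also fixes the contrast: "The treatment effect will be evaluated as the group by time interaction, according to the planned comparisons".

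**Covariates.** The same section adds: "Covariates can also be added to the models, in order to partial out their effects before evaluating the treatment effects". It names no covariate, no outcome to which this applies and no rule for the choice.

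**Pre-admission drinking.** Protocol 4.3 (Inclusion Criteria) requires "Average consumption of 8-30 standard drinks per day for at least 2 weeks prior to enrollment in the study". The clinical status check under 6.2 includes an alcohol history for all admitted patients, and 9.2 (Source Data) keeps eligibility results in the medical record. No numeric CRF field for the value is stated.

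**The concern.** The endpoint is a quantity accumulated over four weeks at home, but the stated test is a change from discharge. A change model normally uses the baseline through its first time point. Here there is no such point: drinking is not scheduled for measurement at D3, and the patient has been an in-patient in detoxification since D1. The one earlier value of the same quantity is drinks per day before admission, and the entry limits allow it to differ almost four-fold between patients (30/8 = 3.75). The plan gives it no committed role.

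Two things are at stake. The first is precision: with 20 patients per arm, any outcome variance explained by prior drinking stays in the error term of an unadjusted level comparison. The second is pre-specification: for an endpoint labelled primary and tested at 0.05, the protocol's wording allows both an unadjusted and an adjusted result and does not say which one counts.

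**Working it through.** **1. The plan's own figure.** Section 10.1 uses a difference of 10 mg, an SD of 10 mg, alpha 0.05 and power 80%. The normal formula gives n = 2 × (1.960 + 0.842)² × (10/10)² = 15.7, so 16 per group, as stated. This is two-sided; one-sided would give 13, and the exact t-test gives 16.7. The figure concerns oxazepam only. The protocol gives no effect, SD or correlation for amount of alcohol.

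**2. Inputs for the alcohol comparison.** n = 20 per arm (40 patients, 1:1); two-sided alpha 0.05. The correlation rho between pre-admission drinks per day and outpatient amount is an assumption, shown as a range.

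**3. Formulas for a between-arm comparison of level.**
- Unadjusted: noncentral t, df = 38, noncentrality d × √(20/2).
- Adjusted for one baseline covariate: df = 37, noncentrality d × √(20/2) / √v, with v = (1 − rho²) × (1 + 1/36). The factor 1 + 1/(2n − 4) = 1 + 1/36 is the small-sample cost of estimating the covariate's slope.

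Example at d = 0.909 and rho = 0.5: the unadjusted noncentrality is 0.909 × 3.162 = 2.87; v = 0.75 × 1.028 = 0.771; the adjusted noncentrality is 2.87 / 0.878 = 3.27.

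| Assumed rho | Power, d = 0.909 (80.0% unadjusted) | Power, d = 0.636 (50.0% unadjusted) | 40/(1 − rho²) |
|---|---|---|---|
| 0 | 78.9% | 48.9% | 40.0 |
| 0.2 | 80.5% | 50.5% | 41.7 |
| 0.3 | 82.5% | 52.6% | 44.0 |
| 0.4 | 85.4% | 55.9% | 47.6 |
| 0.5 | 89.0% | 60.7% | 53.3 |
| 0.7 | 97.2% | 77.2% | 78.4 |

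The last column is the unadjusted total that would match 40 adjusted patients, ignoring the small-sample cost. Adjustment breaks even at a rho between 0.1 (79.3% at d = 0.909) and 0.2, and gains five points or more from about 0.4.

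**4. Chance imbalance.** The between-arm difference in mean prior drinking has a standard error of √(2/20) = 0.32 SD, if allocation is unrelated to prior drinking. A difference of at least 0.5 SD (0.5/0.316 = 1.58 standard errors) arises in about 11% of such trials. In an unadjusted level comparison it shifts the result by rho × 0.5 SD, which is 0.25 SD at rho 0.5.

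**5. The same covariate in the stated test.** With two time points and complete data, the group-by-time term is the difference between arms in mean within-patient change. A covariate that is constant over time and enters as a main effect contributes equally at both times and cancels from that change. It therefore leaves the interaction estimate unchanged and its standard error almost unchanged. The gains in step 3 apply to a level comparison only.

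**The case against.** A reader might infer that the plan rules out adjustment, so that power is certainly lost. The documents do not support that. Section 10.4 calls its model basic and permits covariates, and whether power is lost depends on rho, which is not given. The 8-30 limits restrict the range of the baseline, which tends to lower rho; near zero, adjustment costs about a point.

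A second tempting inference is that an imbalance in prior drinking would pass straight into the planned test. By step 5, a stable difference in level does not do so under the group-by-time interaction. The same argument is the strongest one against the concern: for the test as written, the covariate brings almost nothing. That stands, and it limits the remedy. It does not remove the concern, because the endpoint is an amount over four weeks and no D3 drinking value is scheduled from which to measure change.

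The choice of covariates is commonly left to a statistical analysis plan, which is not shown here, and the data analyst is blinded (10.2.2). This also has force: a failure merely to list covariates would not be a finding. But the protocol itself states the model and the contrast, and these do not fit the endpoint.

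Three limits stand. The documents show that prior drinking is established for eligibility, not that it is stored as a number. The allocation method is not described beyond the 1:1 ratio and electronic execution, so it should not be called simple. The primary status of alcohol amount is not uniform: 2.1 lists it as primary, the synopsis objectives place alcohol use among the secondary aims, and the second primary hypothesis in 10.4 is craving.

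**Conclusion.** The concern holds in a limited form. For amount of alcohol, section 10.4 commits to a group-by-time contrast from D3 although no D3 drinking value is scheduled, leaves adjustment optional and unnamed, and gives no committed role to the one pre-randomisation measure of the same quantity.

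The firm part is the mismatch between endpoint and contrast, together with the open choice between adjusted and unadjusted results. The gain in power is conditional. From an 80% starting point with 20 per arm it is about 0.5 points at rho 0.2, 2.5 at 0.3, 5.4 at 0.4, 9 at 0.5 and 17 at 0.7, against a loss of about one point at rho 0. These figures assume a comparison of level, approximately normal residuals, a linear relation on the analysis scale and all 40 patients with outcome data. They do not apply to the interaction test as written.

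**What to change.** In section 10.4:
- State that the amount of alcohol over the four outpatient weeks is compared between arms as a level, with pre-admission average standard drinks per day as a pre-specified covariate on the same scale as the outcome (for example, both logged).
- State that this comparison replaces the D3-to-D30 group-by-time interaction for this endpoint. Adding the covariate to the interaction model alone would not deliver the gain.
- Limit all other covariates to exploratory analyses.

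In the CRF, record the number of drinks per day and not only that the criterion was met.

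Cost: a few sentences of text, one CRF field for a value already needed at screening, one degree of freedom (38 to 37), and about one point of power if prior drinking turns out to be unrelated to outpatient drinking. No extra visits or patients are needed.

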# STUDY MANAGEMENT

## Investigator Delegation Procedure

The principal investigator is responsible in making and updating a “delegation of tasks” listing all the involved co-workers and their role in the project. He will ensure that appropriate training relevant to the study is given to all of these staff, and that any new information of relevance to the performance of this study is forwarded to the staff involved.

## Protocol Adherence

Investigators ascertain they will apply due diligence to avoid protocol deviations.

All significant protocol deviations will be recorded and reported in the Clinical Study Report (CSR), and in the patient’s CRF or Investigator Site File (ISF) as suitable, following guidelines listed in: http://www.norcrin.no/documents/2013/05/note-to-file.pdf

## Study Amendments

If it is necessary for the study protocol to be amended, the amendment and/or a new version of the study protocol (Amended Protocol) must be notified to and approved by the Competent Authority and the Ethics Committee according to EU and national regulations.

## Audit and Inspections

Authorized representatives of a Competent Authority and Ethics Committee may visit the center to perform inspections, including source data verification. Likewise the representatives from sponsor may visit the center to perform an audit. The purpose of an audit or inspection is to systematically and independently examine all study-related activities and documents to determine whether these activities were conducted, and data were recorded, analyzed, and accurately reported according to the protocol, Good Clinical Practice (ICH GCP), and any applicable regulatory requirements. The principal investigator will ensure that the inspectors and auditors will be provided with access to source data/documents.

